## Abstract

**Background:**

Online information resources and support have been demonstrated to positively influence the well-being of people diagnosed with cancer. This has been explored in past literature for more common cancers; however, for rare cancers, such as neuroendocrine tumors (NETs), there are little to no support or resources available. Despite relatively good prognoses, the quality of life (QoL) of patients with NETs is significantly lower compared with samples of mixed cancer patients and the general population. Patients with NETs also typically report unclear and difficult pathways of disease management and treatment, given the heterogeneity of the diagnosis. There is a vital need to improve the availability of disease-specific information for this patient group and provide supportive care that is tailored to the unique needs of the NET patient population.

**Objective:**

This study described the protocol of a study aimed to better understand the outcomes and experiences of patients diagnosed with NETs and to develop and pilot test a nurse-led online and phone-based intervention that will provide tailored supportive care targeted to NET subgroups (functioning vs nonfunctioning).

**Methods:**

This is a multisite cohort with 3 phases, incorporating both quantitative and qualitative data collection. Phase 1 is a mixed methods prospective cohort study of NET patients identifying differences in patient experiences and priority of needs between NET subgroups. Phase 2 utilizes results from phase 1 to develop an online and nurse-led phone-based intervention. Phase 3 is to pilot test and evaluate the intervention’s acceptability, appropriateness, and feasibility.

**Results:**

Currently, the project is progressing through phase 1 and has completed recruitment. A total of 138 participants have been recruited to the study. To date, patient-reported outcome data from 123 participants at baseline and 87 participants at 6-month follow-up have been collected. Of these, qualitative data from semistructured interviews from 35 participants have also been obtained. Phase 2 and phase 3 of the project are yet to be completed.

**Conclusions:**

Limited research for patients with NETs suggests that QoL and patient experiences are significantly impaired compared with the general population. Furthermore, past research has failed to delineate how the clinical variability between those with functioning and nonfunctioning NETs impacts patient supportive care needs. This study will improve on the availability of disease-specific information as well as informing the design of a nurse-led online and phone-based supportive care intervention tailored for the unique needs of the NET patient population.

**International Registered Report Identifier (IRRID):**

DERR1-10.2196/14361

## Introduction

### Background

It is well established that online information resources and support have a significant impact on the well-being of people diagnosed with cancer [1-3]. To date, there are several tools available for more common cancers, such as breast and prostate cancer, which have a significant impact on the patient experiences of those users [4]. Some of these tools include Internet Cancer Support Groups [5], Comprehensive Health Enhancement Support Systems [6], and bulletin boards [1,7]. More specifically, online information resources and supports were shown to increase hope, universality [1], positive emotions [7], and psychological well-being [5]. However, for those diagnosed with a rare cancer, such as neuroendocrine tumors (NETs), where patients commonly report poorer quality of life (QoL), there are little to no support or resources available [8]. This is even further complicated given that NETs can appear almost anywhere in the body [9]. In addition, NETs can range from being hormone expressive (functioning) and highly symptomatic to nonexpressive (nonfunctioning) and potentially having no symptoms at all [10]. There is an urgent need to better understand the differences in the patient experiences and information and supportive care needs of each NET subgroup (functioning vs nonfunctioning) [8]. These findings can be used to develop online information resources, tools, and support that is tailored to the 2 subtypes of NETs.

NETs are a heterogeneous group of rare cancers that derive from the neuroendocrine cell system [11]. Within Western populations, the incidence of NETs in 2012 was 14.02 per 100,000 according to the Surveillance, Epidemiology, and End Results Program [12]. Although still considered rare, the increasing prevalence of NETs is a worldwide phenomenon [12,13], possibly owing to the detection of early-stage disease and stage migration [14]. With NETs arising across the neuroendocrine system, these malignancies can affect almost any organ; however, they are most commonly found in gastrointestinal sites, typically that of the small intestine, appendix, pancreas, stomach, colon, rectum, and bronchopulmonary sites [15-18].

The clinical presentation and symptom severity of these tumors can vary greatly from patient to patient and, more broadly, between functioning and nonfunctioning NETs. NETs are classified by their secretory potential as functioning or nonfunctioning, depending on their ability to produce peptides that cause distinctive hormonal syndromes such as carcinoid syndrome [9,19,20]. Symptoms associated with functioning NETs are generally those that are caused by the secretion of hormones and those that consequently result in carcinoid syndrome or other secretory syndromes (eg, due to hypersecretion of insulin, gastrin, and glucagon). In the case of carcinoid syndrome, these symptoms largely include flushing of the skin and secretory diarrhea and are highly distressing to patients and have a significant impact on their physical and social functioning [11,21]. In addition, carcinoid syndrome can also result in clinical symptoms such as hypotension or hypertension, bronchoconstriction, and carcinoid heart disease [22]. Compared with patients with a functioning NET, patients with nonfunctioning NETs are often left managing the uncertainty of an asymptomatic cancer [23].

The 5-year survival rates for both functioning and nonfunctioning NETs are estimated at 68% [24], with treatment options varying from surgery, cytotoxic chemotherapy, somatostatin analogs, and targeted biological agents, depending on tumor location and disease stage and grade [25-29]. Despite relatively good prognoses, the QoL of patients with NETs is significantly lower compared with samples of mixed cancer patients and the general population [30-32].

#### Health-Related Quality of Life and Patient Experiences

Research on the patient experience and overall QoL of those diagnosed with NETs is limited in comparison with more common types of cancer such as breast [33], lung [34], and prostate cancer [35,36]. There is, however, evidence to suggest that QoL is significantly impaired in people with NETs when compared with the general population, as assessed by the Euopean Organization for Research and Treatment core, Quality of Life Questionnaire (EORTC QLQ-C30; Role functioning, large-sized difference, 32 points; Social functioning, medium-sized difference, 14 points; and Global QoL, large-sized difference, 18 points) [31,37]. Patients with NETs also score worse on QoL subscales compared with a mixed sample of cancer patients and survivors [30]. The severity and burden of NET-specific symptoms, for example, the frequency of bowel movements and the presence of skin flushing, have been found to correlate with a decrease in overall QoL [38]. Likewise, patients with NETs who are also experiencing symptoms associated with carcinoid syndrome report poorer QoL than patients with NETs who do not have carcinoid syndrome [30]. QoL can also be impacted by the complications of treatment of the disease itself, for example, surgery, somatostatin analogs, chemotherapy, and radiotherapy.

In addition to poorer QoL, a recent qualitative study found that patients with NETs report from their perspective that disease management and treatment pathways are unclear and difficult to navigate. It also highlighted that there is a need for support that is responsive to the specific needs of this group [8]. Indeed, patients with NETs reported low levels of satisfaction with the organization of care, and lower levels of satisfaction were associated with higher levels of anxiety and impaired psychosocial function [39]. Taken collectively, these results indicate the little to no information and support tailored to the unique needs of the NET population.

#### Principles Underpinning the Design of a Patient-Centered Intervention

To address potential differences in unmet needs between NET subgroups, the Schofield and Chambers framework will be used to develop a tailored intervention. This intervention will provide targeted supportive care for patients with NETs according to the clinical characteristics and psychosocial profile of patients with functioning and nonfunctioning NETs.

The Schofield and Chambers framework emphasizes 7 key requisite components to be considered to design and develop an intervention that will be effective, clinically feasible, and sustainable [40]. The framework builds on the Medical Research Council framework for complex interventions, which provides a guideline that can be used to assist with the development and evaluation of health interventions such as targeted supportive care and health information [41]. According to Schofield and Chambers, there are 7 key features required in the development of an intervention to achieve effective and easy translation into usual care: (1) targeting a cancer type and stage, (2) tailoring to individuals’ unique needs, (3) promoting self-management, (4) efficient intervention delivery, (5) ensuring evidence-based and theoretical grounding, (6) specifying protocol training and adherence, and (7) confirming stakeholder acceptability [40].

### Aims and Objectives

The aim of this study is to describe the protocol of the Defining NETs study. The overarching aims of this study are to better understand the outcomes and experiences of patients diagnosed with NETs and to develop and pilot test a nurse-led online and phone-based intervention that provides tailored supportive care targeted to NET subgroups.

More specifically, the objectives of this study are as follows:

To describe and compare the psychosocial (Patient-Reported Outcomes Measurement Information System [PROMIS] short forms assessing anxiety, depression, fatigue, pain interference, pain intensity, sleep disturbance, physical function, satisfaction with social roles and activities, supportive care needs, and experiences of the health care system), QoL (EORTC QLQ-C30 and Gastrointestinal Neuroendocrine QoL Module [GINET21]), and clinical characteristics of patients with functioning and nonfunctioning NETs within 6 months of diagnosis and then again 6 months later;To conduct qualitative interviews to gain a better understanding of the experiences, care preferences, and information needs of patients with NETs;To design and develop an intervention involving online triaging and the delivery of informational resources using multimedia, diagrams, and text, with phone-based nurse follow-up targeted to NET subgroups, as appropriate, and tailored to the individual’s psychosocial and clinical profile;To pilot test the intervention and assess the acceptability and clinical utility of the intervention through a service that is accessible to patients nationwide from both metropolitan and rural areas.

## Methods

### Study Design

A concurrent mixed methods triangulation design will be conducted with 3 phases incorporating both quantitative and qualitative data collection. Both data forms will be used to identify differences in patient experiences and priority of needs between the NET subgroups. Phases are displayed in Figure 1.

**Figure 1 figure1:**
[figure not shown]
Flow chart of study phases. NET: neuroendocrine tumor.

#### Phase 1: Prospective Cohort Study

##### Study Setting

The study will be conducted at 6 sites across Australia. Participatory sites are the Peter MacCallum Cancer Centre in Melbourne, Victoria, with additional recruitment sites at the Royal North Shore Hospital and Northern Cancer Institute (New South Wales), the Lyell McEwin Hospital (South Australia), Royal Brisbane Hospital (Queensland), and the Fiona Stanley Hospital (Western Australia).

##### Eligibility Criteria

Eligibility to this study requires a patient to (1) have a histologically confirmed diagnosis of a NET within the past 6 months, (2) be aged 18 years or older, (3) be able to understand English, (4) have their NET classified as either functioning or nonfunctioning by their treating oncologist, (5) be well enough to participate in the study as determined by the patients’ treatment team, and (6) not demonstrate psychological or cognitive difficulties that would preclude study participation as defined by the treatment team’s cognitive or psychiatric assessment or patient’s disclosed medical history.

A participant will be withdrawn if they (1) become cancer free or (2) withdraw consent. Discontinuation due to adverse events could be either at the request of the participant or the discretion of the investigator(s).

##### Outcomes and Measures

Potentially eligible patients will be identified by their treating clinician and classified as either functioning or nonfunctioning based on their clinical diagnosis. At the time of consent, patients will complete a baseline questionnaire, and thereafter a 6-month follow-up questionnaire. Profiles of the psychosocial, QoL, and clinical characteristics of patients with functioning and nonfunctioning NETs will be developed based on patient-reported outcome data and clinical data extracted from medical records at baseline and 6-month follow-up. Those participants who consent to the opt-in interview will be contacted by the study team to complete a semistructured interview.

The following measures form part of the patient questionnaires:

###### Psychological morbidity, symptoms, and functioning

Emotional Distress Anxiety-Short Form 7a and Emotional Distress Depression-Short Form 8bFatigue-Short Form 7aPain Interference-Short Form 6b and Pain intensity-Short Form 3aSleep Disturbance-Short Form 8bPhysical Function-Short Form 10aSatisfaction with Social Roles and Activities-Short Form 6a

Emotional distress, fatigue, pain, sleep disturbance, physical functioning, and satisfaction with social functioning will be assessed using the PROMIS short forms listed above. Items comprising each short form were first evaluated using classical test theory indices. Unidimensionality was confirmed via confirmatory factor analytic techniques [42], and then, item response theory modeling and expert review were used to identify items measuring the entire spectrum of the construct targeted by each scale. All relevant short forms are standardized, accurate, and efficient self-report measures, and all these short forms were specifically developed for use in clinical oncology research [43].

###### Supportive Care Needs Survey

The Supportive Care Needs Survey (SCNS) is a 34-item questionnaire incorporating 5 scales [44]. These scales assess physical and daily living needs, psychological needs, sexuality needs, patient care and support needs, and health system and information needs. The SCNS demonstrates acceptable reliability and validity [44].

###### Cancer-Specific Health-Related Quality of Life and Gastrointestinal Neuroendocrine Module

The EORTC QLQ-C30 is a 30-item questionnaire incorporating 5 functional scales (physical, role, cognitive, emotional, and social functioning); 3 symptom scales (fatigue, pain, and nausea/vomiting), a global health status scale; and 6 single items assessing dyspnea, sleep disturbance, appetite loss, constipation, diarrhea, and financial impact [45]. Its reliability and concurrent and criterion validity have been demonstrated in numerous studies [45-47].

The QLQ-GINET21 module is a 21-item questionnaire consisting of 5 scales (endocrine, GI treatment, social function, and disease-related worries scale) and 4 single items (muscle/bone pain symptom, sexual function, information/communication function, and body image). The QLQ-GINET21 is a valid tool for assessing QoL in patients with NETs [48].

###### National Health Survey—Cancer Patient Experiences Survey

A total of 21 items have been extracted from the National Cancer Experience Survey used to assess patients’ understanding of their diagnosis and treatment, adequacy of communication, and experiences with hospital staff. These 21 items were adapted for collecting information from patients with functioning or nonfunctioning NETs about their experiences of the health care system following their diagnosis, and this survey was demonstrated to have good content validity [49].

##### Demographics and Clinical Variables

A range of demographic and clinical information will be collected pertaining to the individual’s characteristics (eg, age, gender, language, living arrangements, postcode, occupation, work status, and level of income).

Clinical data collection will occur at baseline and 6 months post baseline and will include a medical record audit to identify clinical information such as date of diagnosis, presence or absence of functional syndrome, primary site, grade, list of and frequency of diagnostic imaging, primary treatment details, length and number of hospital stays, involvement with hospital services, or referrals at the time of recruitment. At follow-up, information pertaining to the participants’ status—alive and disease free, alive with disease, lost to follow-up, or deceased (including date and cause of death and autopsy [if performed])—disease progression/recurrence (including date of detection) and progression-free survival; as well as any additional diagnostic imaging and additional treatments details will be collected.

To further investigate the supportive care needs of patients diagnosed with functioning and nonfunctioning NETs, patients will be asked to participate in an optional semistructured phone interview. Semistructured open-ended questions have been developed to allow participants to share their experiences and preferences.

##### Recruitment

Recruitment will take place from outpatient clinics and chemotherapy day units at participating sites. For each site, a research team will screen and identify new and newly diagnosed patients attending clinics that are potentially eligible. Eligibility will be confirmed with the treating clinician before any approach to clarify details from the medical records. The study will be described, and patients will be provided with a copy of the Participant Information and Consent Form (PICF), a baseline questionnaire, and a reply-paid envelope. Any questions the patient may have will be answered, and the patient will be informed that their involvement in the study is completely voluntary. If the patient wishes to participate, they will be asked to sign the PICF and complete the baseline questionnaire. Similarly, 6-month follow-up questionnaires will be posted out to participants with a reply-paid envelope for participants to return the completed questionnaires in. The study coordinator will call the patient to follow-up the return of these forms if they have not been received after a period of 1 week. Patients who decline to participate will be asked for verbal consent to collect basic demographic and clinical information from their records to examine potential recruitment bias. Reasons for refusal will be recorded.

##### Data Collection Methods

###### Patient Experience Questionnaire

All patient-reported outcome questionnaires will be collected from participants at baseline and again at 6-month follow-up in reidentifiable format and reviewed for completeness of data. Any missing data will be followed up with the participants. The reason for any remaining missing data will be noted on an electronic tracking database.

###### Medical Records Audit

All clinical data to be collected will be written into a paper-based Case Record Form, which will then be entered into an electronic database. Baseline and follow-up clinical data will be collected from the medical records of participating sites.

###### Qualitative Semistructured Interview

Patients will be asked to participate in an optional semistructured phone interview to discuss their experiences, care preferences, and information needs as a person with a NET. This interview will be conducted over the phone by a trained interviewer. On the basis of the aims, semistructured open-ended questions have been developed to allow participants to share their experiences and preferences. Given the semistructured format, additional questions and prompts will be used as necessary, as it is anticipated that themes/issues will be identified during the interview. This will allow the participant to share their individual experiences. It is anticipated that approximately 20 participant interviews will be completed for each NET group, however, to ensure that no more than a feasible amount of patients are recruited to the semistructured interview, the opt-in check box will be removed once enough participants have been recruited to achieve saturation of qualitative data themes.

The duration of the interview will be between 30 and 45 min. The interview will be recorded using a Dictaphone and transcribed verbatim for analysis.

##### Statistical Considerations

###### Sample Size

It is estimated that approximately 170 eligible cases will be seen across all sites over a 17-month recruitment period, with an approximate split of 50% functioning and nonfunctioning NET patients. With 80% consent rate and 10% attrition, this will provide a sample of 136 at baseline and 122 at 6-month follow-up. The expected sample will provide 80% power to detect medium-sized differences between groups on continuous outcomes (0.48 SD at baseline and 0.51 SD at follow-up), assuming a 2-sided, alpha=.05 independent samples *t* test.

###### Quantitative Analysis of Patient-Reported Outcome Measures, Demographics, and Clinical Data

Descriptive statistics will be used to summarize demographic and clinical characteristics and patient-reported outcomes by group at baseline and follow-up. Statistics will include counts and percentages for nominal valued variables and means and standard deviations or medians and interquartile ranges, as appropriate, for continuous valued variables.

Dichotomous valued variables will be compared between groups using Fisher exact test. Nominal valued variables will be compared between groups using Pearson chi-squared test of independence. Responses to patient-reported outcome measures at baseline and follow-up will be compared between groups using independent samples *t* tests; between-groups differences on EORTC QLQ-C30 scales and items will be interpreted using evidence-based guidelines [50]. In the absence of evidence-based guidelines for the SCNS and PROMIS measures, the Cohen d effect size will be calculated and interpreted using existing conventions [51]. If a nonparametric method is required, differences in medians will be examined using the bootstrap percentile method [52]. The number of bootstrap replications will be set at 10,000.

All data will be entered in SPSS version 23 or higher (Chicago, IL), and SPSS will be used for scoring, descriptive analysis, and parametric tests. If a nonparametric method is required, data will be imported into R version 3.3.3 (or higher), and the R package *pairwise CI* will be used for this purpose [53]. Alpha will be set at .05 for all analyses, and all tests will be 2-tailed.

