## Results

Currently, the project is progressing through phase 1 and has completed recruitment. A total of 138 participants have been recruited to the study. To date, we have patient-reported outcome data from 122 participants at baseline and 87 participants at 6-month follow-up. Of these, qualitative data have been collected from 35 participants who consented to a semistructured interview. Phase 2 and phase 3 of the project are yet to be completed.

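### The 6-month t test uses only those who returned the second questionnaire, and no comparison of change is planned; one mixed model per score would improve both at little cost

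*Protocol article*

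**What the plan says.** The section on quantitative analysis fixes the method for the patient-reported scores: "Responses to patient-reported outcome measures at baseline and follow-up will be compared between groups using independent samples" t tests. The fallback is also a between-group comparison: "If a nonparametric method is required, differences in medians will be examined using the bootstrap percentile method". The error rate is common to everything: "Alpha will be set at .05 for all analyses, and all tests will be 2-tailed". No paired, change-score, baseline-adjusted or group-by-visit analysis is named.

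The sample size section uses the same test at each visit. It starts from eligible cases ("It is estimated that approximately 170 eligible cases will be seen across all sites over a 17-month recruitment period"), goes on to "With 80% consent rate and 10% attrition, this will provide a sample of 136 at baseline and 122 at 6-month follow-up", and gives detectable differences of "0.48 SD at baseline and 0.51 SD at follow-up), assuming a 2-sided, alpha=.05 independent samples" t test.

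The first objective under Aims and Objectives is to describe and compare the two groups "within 6 months of diagnosis and then again 6 months later". It does not name change over time.

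On returns, the Results section reports: "To date, we have patient-reported outcome data from 122 participants at baseline and 87 participants at 6-month follow-up". The Abstract gives 123 at baseline, a difference of one that does not affect this point. Under Eligibility Criteria, participants who become cancer free are withdrawn.

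**The concern.** Phase 1 follows one cohort and gives the same questionnaires twice, but the two visits are analysed as if they were unconnected.

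- **Selective loss.** The 6-month t test compares returners with returners. If, say, the less well patients drop out of one group more than the other, the two sets of returners differ for reasons unrelated to the group difference at 6 months. The baseline scores of those lost carry information on this, and the 6-month test ignores them. Loss related to health is built into the design: becoming cancer free ends participation, and death is one of the follow-up statuses to be recorded. The article itself describes the two groups as differing sharply in symptoms, so loss need not act alike in both.
- **No contrast of change.** Two separate tests do not show whether the groups change differently. If one visit were significant and the other not, a reader might take this as evidence of diverging courses, and no planned analysis would support or refute it.

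At stake is the credibility of the 6-month comparison, which is half of the first objective and feeds the intervention content in phase 2.

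**Working it through.** **Reproducing the plan's figures.** 170 × 0.80 = 136 and 136 × 0.90 = 122.4. With equal groups, two-sided 0.05 and 80% power, the t test detects 0.484 SD at N = 136 and 0.511 SD at N = 122, in agreement with the stated 0.48 and 0.51. The normal approximation, used below, gives (1.960 + 0.842) × √(4/N): 0.480 and 0.507.

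**Returns so far.** 1 − 87/122 = 28.7% and 1 − 87/123 = 29.3%, against 10% planned. These counts are interim.

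**Precision with a mixed model.** Let n1 and n2 be the total numbers with baseline and 6-month data, and r the within-person correlation. The documents do not give r; 0.3 to 0.8 is assumed. In SD² units, the variance of the group difference is:

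- 6-month t test: 4/n2
- 6 months, mixed model: 4[(1 − r²)/n2 + r²/n1]
- difference in change, mixed model: 4[(1 − r²)/n2 + (1 − r)²/n1]

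The detectable difference is 2.802 × the square root. The 6-month t test gives 0.507 SD at 136/122 and 0.601 SD at 123/87. The mixed model gives:

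| r | 6 months, 136/122 | 6 months, 123/87 | change, 136/122 | change, 123/87 |
|---|---|---|---|---|
| 0.3 | 0.505 | 0.593 | 0.589 | 0.673 |
| 0.5 | 0.501 | 0.578 | 0.501 | 0.578 |
| 0.6 | 0.498 | 0.568 | 0.449 | 0.521 |
| 0.7 | 0.494 | 0.556 | 0.390 | 0.455 |
| 0.8 | 0.490 | 0.542 | 0.319 | 0.374 |

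For 122/87 and r = 0.6, the change contrast is 2.802 × √(4[0.64/87 + 0.16/122]) = 0.522 SD. A change score in the 87 returners alone would give 2.802 × √(4 × 2 × 0.4/87) = 0.537 SD.

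**Bias of the 6-month t test.** Suppose a proportion p of a group is lost and those lost were g SD worse at baseline than those retained. The retained then sit p × g above their whole group at baseline, and r × p × g above it at 6 months if loss depends on the baseline score. The bias in the group difference is r(p₁g₁ − p₂g₂).

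- Equal loss, equally related to health (p₁ = p₂, g₁ = g₂): bias 0, however strongly loss depends on health.
- Assumed loss of 40% and 18% (average 29%, matching the interim total), the same g in both groups, r = 0.6: 0.6 × 0.5 × 0.22 = 0.066 SD for g = 0.5, and 0.6 × 1.0 × 0.22 = 0.132 SD for g = 1.0.
- Same loss with other r: at g = 0.5 and r = 0.3, 0.3 × 0.5 × 0.22 = 0.033 SD; at g = 1.0 and r = 0.8, 0.8 × 1.0 × 0.22 = 0.176 SD.

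A simulation of a different pattern, with loss depending on baseline in one group only (logit slope 1 per SD, r 0.5 to 0.7), gave a bias of 0.06 to 0.08 SD when loss at the average baseline score was set at 10%, and 0.13 to 0.19 SD at 29%. Estimation that also used the baselines of those lost gave a bias near 0 in each case, as it should when loss depends only on baseline. The documents give no return rates by group, so all these bias figures are illustrations.

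**The case against.** The best defence is that the plan answers the question it sets. The objective asks for a comparison at each of two times, the t tests give exactly that, and the sample size matches and reproduces. This stands, and it rules out some stronger readings:

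- A reader might infer that the baseline data of people lost are thrown away. They are not: every baseline respondent enters the baseline test. Only the 6-month comparison ignores those values.
- A reader might infer that the prospective design is wasted. Change is not a stated objective, and follow-up also supplies vital status, progression and treatment data.
- A reader might infer that the 6-month test is valid only if return is unrelated to health. The formula above shows otherwise: the bias needs loss that relates to health differently in the two groups.
- A reader might take 29% as the final attrition. The article reports counts to date with phase 1 still in progress, and some 6-month forms may not yet have been due.

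The article also limits missing data: the coordinator calls after a week, gaps are pursued with participants, and reasons are recorded. The full protocol or an analysis plan may add sensitivity analyses. But the article does name the method for the 6-month comparison, and these steps cannot recover people who have been withdrawn.

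Finally, a mixed model is no complete cure. Becoming cancer free happens after baseline, so the resulting loss need not be explained by the baseline score. That limits the benefit, but the t test is no better placed.

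**Conclusion.** The point holds in limited form. The 6-month t test is a completers-only comparison, exposed to bias if loss acts differently in the two groups, and no comparison of change is planned although the data for one are collected.

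The precision argument is weak: a gain of at most 0.017 SD in detectable difference at planned attrition (0.507 − 0.490), and of about 0.01 to 0.06 SD at the interim counts (0.601 − 0.593 to 0.601 − 0.542). The argument from selective loss is stronger but conditional: nothing if loss is alike in both groups, about 0.07 to 0.13 SD under the assumed 40% against 18% with r = 0.6. The upper value is about a quarter of the 0.51 SD design difference (0.132/0.51 = 26%). A change contrast would be detectable at about 0.52 SD at r = 0.6 and 122/87.

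All of this rests on an assumed correlation and an assumed pattern of loss. It is a worthwhile, inexpensive improvement to the plan, not a flaw that invalidates it.

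**What to change.** Replace the visit-wise t tests with one linear mixed model per score:

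- fixed effects for group, visit and group × visit, with an unstructured covariance for the two visits;
- all participants with at least one questionnaire included;
- baseline means left free to differ, because the groups are not randomised;
- reported with 95% confidence intervals: the group difference at each visit, and the difference in change as a secondary contrast.

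Keep the bootstrap of medians for markedly skewed scores and single items, and state that those 6-month comparisons remain based on returners only.

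State two limits. The model assumes that data are missing at random given the observed scores, so it does not correct loss driven by unobserved events after baseline. For participants withdrawn as cancer free, it estimates scores as if they had stayed in the study. Tabulating return rates and reasons for loss by group would let readers judge how much this matters.

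The cost is a change of wording and a little more analysis time. The model runs in SPSS, which the article already names, and needs no further data. The sample size statement can stand, since the model's detectable 6-month difference is no larger than the t test's. The change is best recorded before the 6-month groups are compared.
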